**1.3 What is the definition of an unanticipated problem?**

Do not change this answer

An unanticipated problem is any event, experience that meets ALL 3 criteria below:

- Is unexpected in terms of nature, severity or frequency given the research procedures that are described in the protocol-related documents AND in the characteristics of the subject population being studies
- Related or possibly related to participation in research. This means that there is a reasonable possibility that the incident may have been caused by the procedures involved in the research study.
- The incident suggests that the research placed the subject or others at greater risk of harm than was previously known or recognized OR results in actual harm to the subject or others
  1. **What are the definitions of a protocol violation and/or noncompliance?**

Do not change this answer

**A protocol violation is defined as any change, deviation, or departure from the study design or procedures of research project that is NOT approved by the IRB-HSR prior to its initiation or implementation.** Protocol violations may be major or minor violations.

**Noncompliance can be a protocol violation OR deviation from** standard operating procedures, Good Clinical Practices (GCPs), federal, state or local regulation**s.** Noncompliance may be serious or continuing.

Additional Information: see the IRB-HSR website at

<http://www.virginia.edu/vpr/irb/HSR_docs/Forms/Protocol_Violations_%20Enrollment_Exceptions_Instructions.doc>

- 1. **If pregnancy occurs how will this information be managed?**

_____ Adverse Event- will follow adverse event recording and reporting procedures outlined in section 3.

_____ Unanticipated Problems- will follow Unanticipated Problem recording and reporting procedures outlined in section 3.

__X___ Other: Document in research records and subject participation will be discontinued at that time

- 1. **What is the definition of a Protocol Enrollment Exception?**

__X___NA- No outside sponsor

- 1. **What is the definition of a data breach?**

Do not change this answer

A data breach is defined in the HITECH Act (43 USC 17932) as an unauthorized acquisition, access, or use of protected health information (PHI) that compromises the security or privacy of such information.

Additional Information may be found on the IRB-HSR Website: [Data Breach](http://www.virginia.edu/vpr/irb/hsr/data_breach.html)

###### 2. Identified risks and plans to minimize risk

**2.1 What risks are expected due to the intervention in this protocol?**

| **Expected Risks related to study participation.** | **Frequency** |
| --- | --- |
| Ecchymosis, hematoma, venous thrombosis or infection at the I.V. site  Fitness tests may cause anxiety and/or claustrophobia  During FMD, subjects may experience mild discomfort (e.g. mild pain, tingling, and/or numbness) in their forearm and/or hand as a result of the prolonged inflation (5 min.) of the blood pressure cuff required for the procedure. | ____Occurs frequently  ____Occurs infrequently  ___x_Occurs rarely  ____Frequency unknown |
| Reproductive Risks | Minimized due to the requirements of this protocol. |
| Violation of subject’s privacy and confidentiality | Minimized due to the requirements of the privacy plan in this protocol |
| Cardiovascular reactions to exercise, such as fainting, syncope, chest pain, or sudden cardiac death. | Occurs rarely (risk of cardiac events during exercise testing: 3/5,000 tests; risk of death during exercise: ~1/18,000 individuals per year) |

**2.2 List by bullet format a summary of safety tests/procedures/observations to be performed that will minimize risks to participants:**

- A careful history and physical examination to exclude those subjects with a history or current symptoms of cardio-pulmonary conditions as well as renal, liver or metabolic disease.
- InBody will be performed by trained personnel
- CBC with differential to screen out people with low hematocrit or evidence of infection or other illness
- Glucose and HbA1c to assess diabetes status
- Comprehensive Metabolic to evaluate kidney and liver function.
- Pregnancy test in females
- Thorough physical examination and medical history will be performed by a physician prior to study entry, with specific attention to exclude those subjects with a history or current symptoms of cardio-pulmonary conditions.
- Liver, kidney, and hematologic function will be assessed from blood samples using standard clinical tests listed below:

CBC, BUN, and creatinine, tests within normal limits

Liver function tests no greater than 3-fold within normal limits

HCT for women > 36%, Men >38%

- Complications of I.V. cannuale will be minimized by aseptic and skilled nursing technique
- The minimal amount of blood required to measure each lab will be removed.
- Each exercise test will be monitored by Exercise Physiology Core Lab personnel who have current training in CPR and AED use, and all protocols will follow the American College of Sports Medicine Guidelines. An AED and a cell phone available to call the code 12 team if necessary. While a physician is not required to be present during exercise testing in this population (according to AHA/ACC/ACSM guidelines), it is standard CRU practice that the study physician is aware of the test and available by page.
- If a subject develops leg pain during the cycle ergometer exercise, the resistance on the device will be decreased.

**2.3 Under what criteria would an INDIVIDUAL SUBJECT’S study treatment or study participation be stopped or modified**

__X___At subject, PI or sponsor’s request

- If subject has any of the less likely to severe side effects for a particular admission that study will be terminated, and depending on the side effect and extent may be excluded from all admissions.
- Any significant blood loss is prevented by regular visual inspection of the catheter insertion site and removing a catheter and applying pressure if there is obvious extravasation of blood into the tissue.
- These catheters are in place for a brief time (~five hours) and careful aseptic technique is used for catheter placement. With these precautions infections secondary to intravenous lines is extremely uncommon. Should an infection occur, we would treat with oral or intravenous antibiotics or if necessary by local drainage.
- If the subject experiences headache, chest pain, vomiting, flushing, or dizziness
- If the subject experiences hypoglycemia with a blood glucose of 60 or less the study will be stopped. It may be stopped at a higher value at the discretion of the Principal Investigator if there is loss of IV access.
- A woman with a positive pregnancy test will be excluded.
- **Exercise Testing**

The ACC/AHA guideline update for exercise testing endorsed by the ACSM is used in the Exercise Physiology Core Laboratory for all exercise protocols. This document provides guidelines for absolute and relative indications for terminating exercise testing (documentation accompanies this submission)

*Exercise Termination:*

Absolute

1. Drop in systolic blood pressure of >10 mm Hg from baseline blood pressure despite an increase in workload, when accompanied by other evidence of ischemia
2. Moderate to severe angina
3. Increasing nervous system symptoms (e.g. ataxia, dizziness, or near syncope)
4. Signs of poor perfusion (cyanosis or pallor)
5. Technical difficulties monitoring the ECG or systolic blood pressure
6. Subject’s desire to stop
7. Sustained ventricular tachycardia
8. ST elevation (>1.0 mm) in leads without diagnostic Q-waves other than V1 or aVR.

Relative

1. Drop in systolic blood pressure of >10 mm Hg from baseline blood pressure despite an increase in workload, in the absence of other evidence of ischemia.
2. ST or QRS changes such as excessive ST depression (>2mm horizontal or down-sloping ST-segment depression) or marked axis shift
3. Arrhythmias other than sustained ventricular tachycardia, including multifocal PVC’s triplets of PVC’s, supraventricular tachycardia, heart block, or bradyarrhythmias.
4. Fatigue, shortness of breath, wheezing, leg cramps, or claudication
5. Development of bundle-branch block or intraventricular conduction delay that cannot be distinguished from ventricular tachycardia
6. Increasing chest pain
7. Hypertensive response: systolic >250 mm Hg, diastolic >115 mm Hg.
   1. **Under what criteria would THE ENTIRE STUDY need to be stopped.**

__X___Per IRB, PI, DSMB, or sponsor discretion

**2.5 What are the criteria for breaking the blind/mask?**

__X___NA – Not blinded/masked

- 1. **How will subject withdrawals/dropouts be reported to the IRB prior to study completion?**

__X___IRB-HSR continuation status form

###### 3. Adverse Event / Unanticipated Problem Recording and Reporting

**3.1 Will all adverse events, as defined in section 1.1, be collected/recorded?** NO

**►IF NO, what criteria will be used?**

__X___Only adverse events deemed related/possibly related to study

**3.2 How will adverse event data be collected/recorded**?

__X___Spreadsheet: paper or electronic

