# Data and Safety Monitoring Plan

###### 1. Definition:

**1.1 How will you define adverse events (AE)) for this study?**

Check **all** that apply

__X___An adverse event will be considered any undesirable sign, symptom or medical or psychological condition **even if the event is** **not considered to be related** to the investigational drug/device/intervention. Medical condition/diseases present before starting the investigational drug/intervention will be considered adverse events only if they worsen after starting study treatment/intervention. An adverse event is also any undesirable and unintended effect of research occurring in human subjects as a result of the collection of identifiable private information under the research. Adverse events also include any problems associated with the use of an investigational device that adversely affects the rights, safety or welfare of subject s.

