**3.3. How will AEs be classified/graded?**

_X_ Serious/Not serious

- 1. **What scale will the PI use when evaluating the relatedness of adverse events to the study participation?**

__X___The PI will determine the relationship of adverse events to the study

using the following scale:

Related: AE is clearly related to the intervention

Possibly related: AE may be related to the intervention

Unrelated: AE is clearly not related to intervention

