**5.3. What items will be included in the aggregate review conducted by the PI?**

Check all that apply.

__X___All adverse events

__X___Unanticipated Problems

__X___Protocol violations/Issues of noncompliance

- 1. **How often will aggregate review occur?**

For additional information on aggregate review see: [www.virginia.edu/vpr/irb/hsr/continuations.html#aggreview](http://www.virginia.edu/vpr/irb/hsr/continuations.html#aggreview)

__X___Annually

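### Adverse events judged unrelated are kept out of the record, so the stated review of all adverse events cannot be done and the serious-event reporting rule does not fit

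*Protocol*

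**What the plan says.** All references are to the Protocol. Unless stated otherwise, section numbers are those of the Data and Safety Monitoring Plan.

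- **Definition (1.1).** "An adverse event will be considered any undesirable sign, symptom or medical or psychological condition", including events "not considered to be related" to what is being studied.
- **Recording (3.1).** The form asks "Will all adverse events, as defined in section 1.1, be collected/recorded" and the answer is NO. The criterion then ticked is "Only adverse events deemed related/possibly related to study". Section 3.2 names a spreadsheet as the place of recording.
- **Who judges, and on what scale (the item after 3.3).** "The PI will determine the relationship of adverse events to the study". The first category reads "Related: AE is clearly related to the intervention". The other two labels, for possibly related and unrelated events, also refer to the intervention.
- **Masking (2.5).** "Not blinded/masked".
- **Start of recording (3.5).** Recording begins once a subject starts the intervention, a study procedure or specimen collection.
- **Reporting to the IRB (3.7).** Internal events that are serious and unexpected go to the IRB within 7 calendar days. That row sets no condition on relatedness.
- **Oversight (5.1, 5.3 and the item after it).** No body other than the PI oversees the safety data. The PI's aggregate review is annual and lists "All adverse events".

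**The concern.** Relatedness is normally an attribute of a recorded event. Here it decides whether the event is recorded at all, and the person deciding knows the assignment.

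Two things are at stake. The first is whether the safety procedures that the protocol describes can be carried out from the record it creates. The second is whether the filter works equally in the two bariatric arms: exercise plus standard care has an added study intervention to which an event might be attributed, and standard care alone does not. Because the filter acts before recording, an event it removes cannot be recovered at analysis, so a statistical analysis plan could not repair this.

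**Working it through.** The protocol states no AE rate or count, so there is no figure to reproduce. The check sets the provisions side by side.

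**1. Section 3.1 against section 5.3.** Under 3.1 the spreadsheet holds events judged related or possibly related. Under 5.3 the PI reviews all AEs in aggregate. Events judged unrelated are AEs under 1.1 but are not on the spreadsheet, so the review cannot reach them. An excess of events that were each judged unrelated would not show up.

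**2. Section 3.1 against section 3.7.** Take a serious, unexpected event judged unrelated. Section 3.7 requires a report within 7 calendar days; section 3.1 keeps the event off the record. The missing relatedness condition in that row looks deliberate, because the row above it, for deaths, does state one.

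**3. The criterion against the scale.** Section 3.1 filters on relatedness to the study. The question that introduces the scale asks about study participation, and the sentence that answers it refers to the study. The three labels refer to the intervention. Section 3.5 brings study procedures and specimen collection into scope. An IV-site haematoma, which section 2.1 expects as a rare risk, is related to the study, but none of the three labels fits it properly. Taken literally it is clearly not related to the intervention, and so it would go unrecorded.

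**4. A category with no place in the record.** The scale provides for unrelated events. Under 3.1 these are exactly the events left out.

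**5. Whether the filter depends on arm.** Under Phase 4: Interventions, bariatric subjects receive standard care alone or exercise plus standard care for 4 weeks. Let *r* be the true rate of some type of event, equal in both arms, and let *q* be the probability that the PI judges such an event at least possibly related. Then

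- recorded rate, exercise: *r* × *q*(Ex)
- recorded rate, standard care: *r* × *q*(SC)
- difference caused by recording alone: *r* × [*q*(Ex) − *q*(SC)]

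Two readings bound the effect in direction:

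- *The labels govern (intervention).* Standard care has no added study intervention, so *q*(SC) tends towards zero for every type of event.
- *The criterion governs (study).* The bariatric schedule gives both arms the same treadmill test, IV catheter, meal test, vascular tests and optional pre-intervention biopsy. For events tied to these, *q* should be about the same in both arms and the difference about zero. For other events, such as dizziness or joint pain between visits, *q*(Ex) can still exceed *q*(SC), because the PI knows who is exercising.

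The protocol gives neither *r* nor *q*, so the direction follows from the wording but the size does not.

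**6. How far this reaches.** Both non-bariatric arms receive an active study intervention (diet, or diet plus exercise), so the argument in step 5 is weaker there; steps 1 to 4 apply unchanged. Phase 6: Bariatric Surgery has the team look at any complications of surgery, with no relatedness condition, so that part of the second primary objective is not touched.

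**The case against.** The best defence is that section 3.1 is an openly declared restriction. It cites 1.1, answers NO and names the criterion. Defining a term broadly and recording a subset is not a contradiction, and a reader who infers a conflict between 3.1 and 1.1 goes further than the text allows. That part of the defence stands.

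Other parts also stand, and they limit the point:

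- The criterion in 3.1 is relatedness to the study. A reader might infer from the labels that only events caused by the intervention count, and hence that standard care can contribute almost nothing. The text does not settle that, and events from shared procedures can qualify in either bariatric arm.
- A reader might extend the arm imbalance to diet against standard care. Diet is given only to non-bariatric subjects, who are compared with diet plus exercise, so no such comparison exists.
- A reader might take the annual review to be the only safety oversight. It is not: 3.7 sends serious, unexpected events to the IRB, 2.3 sets criteria for stopping individual participation, and the item after it gives the IRB discretion to stop the study.
- The outcome lists under Statistical Considerations include no between-arm comparison of AEs, so no planned result is shown to be biased.

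It can also be said that section 5.3 means all recorded events. That is possible, but then the review is narrower than its label and still cannot see events judged unrelated. It does nothing for the conflict with 3.7 or for the mismatch between criterion and labels.

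**Conclusion.** The point holds in this form. As written, section 3.1 cannot supply the aggregate review described in 5.3, does not fit the serious and unexpected row of 3.7, and rests on a scale whose labels do not match either the criterion in 3.1 or the scope in 3.5. These conclusions rest on the wording alone.

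The arm imbalance is a reasonable inference, confined to exercise against standard care in the bariatric cohort and, if relatedness to the study governs, to events not tied to shared procedures. It assumes that an unmasked PI more readily attributes an event to a study intervention where there is one. That comparison is small: the sample size justification plans 8 subjects per bariatric group. No magnitude can be given.

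The change should be made before recording continues under the present rule. It does not threaten the metabolic objectives, but the safety review cannot be carried out as stated, and events left out cannot be restored later.

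**What to change.** 1. Change the answer in 3.1 so that every AE meeting the definition in 1.1 is recorded for every subject in every arm.
2. Record relatedness and seriousness as attributes of each entry. Reword the three labels so that relatedness means relatedness to study participation, covering both procedures and the assigned intervention.
3. State that the review in 5.3 and the reports under 3.7 draw on this full record. Leave what must be reported to the IRB, and when, as it is.
4. Summarise all AEs, and related AEs as a subset, by arm.

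The cost is one changed answer, a few aligned phrases and additional spreadsheet lines. Under Human Participants, the number treated is 28 + 16 = 44 from the cohort figures, or 50 from the stated total, so the added work is small.

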**3.3. How will AEs be classified/graded?**

_X_ Serious/Not serious

- 1. **What scale will the PI use when evaluating the relatedness of adverse events to the study participation?**

__X___The PI will determine the relationship of adverse events to the study

using the following scale:

Related: AE is clearly related to the intervention

Possibly related: AE may be related to the intervention

Unrelated: AE is clearly not related to intervention

**3.5 When will recording/reporting of adverse events/unanticipated problems begin?**

__X___After subject begins study drug/ device placement/intervention /study-related procedure/specimen collection

**3.6 When will the recording/reporting of adverse events/unanticipated problems end?**

__X___ End of study drug/device/intervention/participation

**3.7 How will Adverse Events, Unanticipated Problems, Protocol Violations and Data Breaches be reported? Complete the table below to answer this question**

| **Type of Event** | **To whom will it be reported:** | Time Frame for Reporting | How reported? |
| --- | --- | --- | --- |
| **Any internal event resulting in death that is deemed DEFINITELY related to (caused by) study participation**  *An internal event is one that occurs in a subject enrolled in a UVa protocol* | IRB-HSR | Within 24 hours | IRB Online and phone call  [www.irb.virginia.edu/](http://www.irb.virginia.edu/) |
| **Internal, Serious, Unexpected adverse event** | IRB-HSR | Within 7 calendar days from the time the study team received knowledge of the event.  *Timeline includes submission of signed hardcopy of AE form.* | IRB Online  [www.irb.virginia.edu/](http://www.irb.virginia.edu/) |
| **Unanticipated Problems** that are not adverse events or protocol violations  This would include a Data Breach. | IRB-HSR | Within 7 calendar days from the time the study team received knowledge of the event. | Unanticipated Problem report form.  [*http://www.virginia.edu/vprgs/irb/HSR_docs/Forms/Reporting_Requirements-Unanticipated_Problems.doc*](http://www.virginia.edu/vprgs/irb/HSR_docs/Forms/Reporting_Requirements-Unanticipated_Problems.doc) *)* |
| **Protocol Violations/Noncompliance**  *The IRB-HSR only requires that MAJOR violation be reported, unless otherwise required by your sponsor, if applicable.*  *.* | IRB-HSR | Within 7 calendar days from the time the study team received knowledge of the event. | Protocol Violation, Noncompliance and Enrollment Exception Reporting Form  [*http://www.virginia.edu/vprgs/irb/hsr_forms.html*](http://www.virginia.edu/vprgs/irb/hsr_forms.html)  *Go to 3^rd^ bullet from the bottom.* |
| **Data Breach** | The UVa Corporate Compliance and Privacy Office  ITC: if breach involves electronic data  Police if breach includes items that are stolen:  Stolen on UVA Grounds  OR  Stolen off UVa Grounds- contact police department of jurisdiction of last known location of PHI | As soon as possible and no later than 24 hours from the time the incident is identified.  As soon as possible and no later than 24 hours from the time the incident is identified.  IMMEDIATELY. | UVa Corporate Compliance and Privacy Office- [contact]  **ITC:**  [Information Security Incident Reporting procedure](https://policy.itc.virginia.edu/policy/policydisplay?id=IRM-012), <http://www.itc.virginia.edu/security/reporting.html>  UVa Police-Phone- [contact] |

**4.** **How will the endpoint data be collected/recorded.** Check all that apply

__X___Source documents

**5. Data and Safety Oversight Responsibility**

**5.1. Who is responsible for overseeing safety data for this study?**

INSTRUCTIONS:

e.g. Who is looking at data in aggregate form to identify trends?

Check all that apply

__X___No additional oversight body other than PI at UVa Skip question 5.2

**5.2. What is the composition of the reviewing body and how is it affiliated with the sponsor?** N/A

**5.3. What items will be included in the aggregate review conducted by the PI?**

Check all that apply.

__X___All adverse events

__X___Unanticipated Problems

__X___Protocol violations/Issues of noncompliance

- 1. **How often will aggregate review occur?**

For additional information on aggregate review see: [www.virginia.edu/vpr/irb/hsr/continuations.html#aggreview](http://www.virginia.edu/vpr/irb/hsr/continuations.html#aggreview)

__X___Annually

